#### Control group

Participants in the control group only will receive a biweekly newsletter by email without feedback. They will be provided with material and instructions to self-record their daily meals and exercise. The newsletter only will content basic information about nutrition and exercise.

Follow-up sessions will take place in three arms to assess the adherence to the interventions and to evaluate the main objective of this study, the acquirement of long-term healthy habits. These face-to-face sessions will last between 15 and 30 min and will take place 1, 3, 6 and 12 months after the post treatment session. In this follow-ups, we will review: anthropometric measures, quality of life, nutrition and exercise habits.

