### Outcomes

#### Primary outcomes measures

The primary outcome is the weight loss. First, differences between the pre and post measures for each treatment arm. Treatment success is defined as 5–10% of weight loss respect the initial weight. Then, significant differences in weight loss and other anthropometric measures, specified later, between the three treatment arms. Finally, the maintenance of weight loss during the follow-ups, significant differences between the three treatment arms.

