### Study design and randomization

#### Procedure

Participants will be recruited through advertising (flyers, posters, University website, workplace-based emails and social networks). Obese and overweight people interested in participating in the study must send an email to the coordinator of the project. Participants will receive an email to attend an appointment with a psychologist. In this first appointment, patients will be informed about the aims and characteristics of the study, they must sign the written informed consent and, after that, a brief interview and baseline anthropometric measures will be taken. Anthropometric measures will be weight, height; and, neck, chest, waist, hips, leg and arm circumferences. All measures will be taken with the participant wearing light clothing and without shoes. Height will be taken with 1 cm using a stadiometer. Weight will be measured on a digital scale. Circumferences measurements will be measure following the indications provided by WHO [33].

To ensure the accomplishment of inclusion and exclusion criteria participants must answer a large battery of questionnaires specified later. These questionnaires are divided in two batches. After the first in-person appointment, participants will receive an email with the instructions to complete the first batch of questionnaires, they will be provided with an identity number for data protection and with the direct link to the available questionnaires in the platform SurveyMonkey. After the completion of the first part, a second email with the link to the second batch of questionnaires will be sent.

Assessment phase will last 2 weeks, selected participants will be randomized to one of the three study arms. Patients will receive an email with information about their belonging group. Obese and overweight people randomized to *“en_línea”* program, must assist to a 1 h training session to get familiar with the website and the mobile application. When participants are included in the study, both *en_línea* and group intervention, they will be given timings for follow-up meetings during the treatment at week 8 and week 17. After interventions finish, follow-up meetings will be happened at 1, 3, 6 and 12 months. In the follow-up visits a brief interview and anthropometric measures will be taken again, the duration of these meeting will be between 15 and 30 min (Fig. 3).

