### Statistical analysis

To estimate the sample size has been used the primary outcome, weight loss differences between baseline and post-treatment measures. The range of the effect size of the intervention will be 0.5 SD in group comparisons, alpha 5% and two-tail tests [51]. These data determine that we need at least 88 patients per group, considering an expected 31% dropout rate [52], our final choice will be *N* = 305 [53].

Analysis will be performed using STATA/IC 14.2. All data will be checked for missing values, accuracy and normality criteria. Intention to treat analysis (ITT) will be used to analyze the data, including all randomized participants. After that, per protocol analysis will be performed for participants who have completed 17 weeks follow-up. ANOVA for repeated measures, with type of intervention as independent variable and time (baseline and follow-up visits) as dependent variable, will be conducted to analyze primary and secondary outcomes.

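### The primary outcome lists within-arm changes, six circumferences and follow-up maintenance beside weight loss, with no lead comparison, and is wider than both the abstract and the endpoint used for the sample size

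*Protocol article*

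**What the plan says.** The Primary outcomes measures section opens plainly: "The primary outcome is the weight loss". Three further items follow under the same heading.

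- Within arms: "First, differences between the pre and post measures for each treatment arm".
- Between arms: "Then, significant differences in weight loss and other anthropometric measures, specified later, between the three treatment arms". The measures are given in the Procedure section: "Anthropometric measures will be weight, height; and, neck, chest, waist, hips, leg and arm circumferences". Height is not a response measure in adults, so this means weight plus six circumferences.
- Over time: "Finally, the maintenance of weight loss during the follow-ups, significant differences between the three treatment arms". According to the Control group section, the follow-up sessions "will take place 1, 3, 6 and 12 months after the post treatment session", in all three arms.

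Two other places describe the primary outcome more narrowly. The Methods part of the abstract gives post-treatment weight loss and its maintenance, with no circumferences and no within-arm change. The Statistical analysis section equates the primary outcome with "weight loss differences between baseline and post-treatment measures" and sizes the trial on it, with an effect of 0.5 SD, alpha 5% and two-tailed tests. That sentence is the only place where an alpha appears. The same section assigns a repeated-measures ANOVA to primary and secondary outcomes alike.

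**The concern.** The choice of primary outcome belongs to the protocol, and this article gives it three different scopes. A separate analysis plan could add a multiplicity rule, but it would first have to decide which scope to apply it to.

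Two consequences matter. First, with no lead measure, contrast or time point, the result presented as primary could be chosen after the data are seen. Secondly, the item listed first compares each arm with itself. Participants are volunteers recruited by advertising, and even the controls receive a nutrition and exercise newsletter and material for recording meals and exercise. Weight could therefore fall in all three arms without any advantage for en_línea. The Background section states the aim as a comparison with group therapy and with control, and a within-arm change cannot answer that.

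**Working it through.** **1. The plan's own figure.** The formula for n per group is 2(z₁₋α/₂ + z₁₋β)² / d², with d = 0.5 and two-sided α = 0.05.
- 80% power: 2(1.960 + 0.842)² / 0.25 = 62.8, so 63.
- 90% power: 2(1.960 + 1.282)² / 0.25 = 84.06, so 85.
- The stated 88 per group corresponds to about 91% power. The article does not state a power.

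The 88 is therefore consistent with one two-arm comparison of one measure at an unadjusted 5%. The step from 88 per group with 31% dropout to N = 305 does not follow (3 × 88 / 0.69 = 383), but that is a separate matter and does not decide this point.

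**2. The three descriptions side by side.**

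| Place | Weight, post-treatment | Maintenance | Circumferences | Within-arm change |
|---|---|---|---|---|
| Abstract, Methods | yes | yes | no | no |
| Primary outcomes measures | yes | yes | yes | yes |
| Statistical analysis (sample size) | yes | no | no | no |

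**3. What is listed as primary.** Counting one three-arm test per item:
- within-arm pre-post change: 3;
- between-arm differences post-treatment: 7 measures (weight and six circumferences);
- maintenance: 4 visits, weight only.

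The sum is 3 + 7 + 4 = 14, of which 11 are randomised comparisons. With three pairwise contrasts per between-arm item it is 3 + 21 + 12 = 36, of which 33 are randomised. The article does not fix this count. A repeated-measures ANOVA of weight could cover several visits in one group-by-time test.

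**4. False-positive rate if the listed between-arm items were tested at 5% without adjustment.** This was simulated under the null hypothesis (2 million runs per setting): three arms of equal size, m measures with a common correlation r. An omnibus result counts when the three-arm chi-square on 2 df exceeds its 95% point. A pairwise result counts when any |z| exceeds 1.96. The article gives no correlations, so r = 0.5 to 0.9 is an assumption.

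| Items tested | r | Omnibus | Pairwise |
|---|---|---|---|
| Weight only (m = 1) | – | 5.0% | 12.2% |
| Weight + 6 circumferences (m = 7) | 0.5 | 23.4% | 47.4% |
| | 0.7 | 18.4% | 38.0% |
| | 0.8 | 15.3% | 32.4% |
| | 0.9 | 11.7% | 25.6% |

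The two en_línea contrasts on weight alone, unadjusted, give 9.1%. Adding weight at four follow-ups as separate tests (m = 11) gives 31% to 14% omnibus and 59% to 29% pairwise, for r = 0.5 to 0.9. These last figures apply only if each visit is tested on its own.

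**5. After the fix.** In a fixed sequence the second contrast is tested only if the first is significant, so the error over both stays at 5%. Power for the first contrast is Φ(0.5√(n/2) − 1.96): 91.3% with 88 evaluable per group, and 84.1% with 70. The figure of 70 is what N = 305 leaves after 31% dropout (305 × 0.69 / 3 = 70.15).

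**The case against.** The other side has several good points.

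- **A reader might infer that every component is tested at 5%.** The article does not say so. Its one alpha belongs to the sample-size sentence, and an analysis plan that is not shown may hold a multiplicity rule. The error rates above are therefore conditional.
- **A reader might take the pairwise figures as those of the plan.** The named method is a repeated-measures ANOVA, and the text speaks of differences between three arms. Both fit an omnibus test, which holds weight alone at 5.0% and roughly halves the range for seven measures.
- **A reader might infer that one significant circumference, or one within-arm change, would count as primary success.** No rule says that any single item suffices. The section opens with weight loss, treatment success is defined as a percentage of weight lost, and the follow-up item concerns weight only. The Background section states the hypothesis and primary aim as comparisons between arms.
- **Maintenance has a claim to primary status.** The abstract and the primary aim both include it, so moving it to secondary would change the objective of the trial.

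All four stand, and they limit the size of the point and shape its remedy. They do not remove it: an ANOVA of weight does not cover six circumferences, and a comparative aim elsewhere does not explain why within-arm change is listed first as primary.

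**Conclusion.** The point holds as a stated inconsistency. The primary section is wider than the abstract and wider than the single endpoint that the trial is sized on; it includes a comparison that randomisation does not protect; and it names no lead measure, contrast or time point.

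The possible inflation for the seven post-treatment measures is about 12% to 23% with omnibus tests, or 26% to 47% with pairwise tests. Both ranges rest on assumed correlations of 0.9 to 0.5 and on no adjustment being made. For weight alone, an omnibus test has no inflation and unadjusted pairwise tests give 12.2%. The documents do not support the claim that the plan will run at these rates. They do support the claim that nothing in the article prevents it. The matter should be corrected before analysis.

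**What to change.** Name one primary outcome that matches the sample-size sentence: the between-arm difference in weight change from baseline to week 17. Control the error over its contrasts at two-sided 5%. One way is a fixed order: en_línea versus control, then en_línea versus group therapy only if the first is significant. Alternatives are pairwise tests only after a significant three-arm test, or Bonferroni over the two en_línea contrasts, for which 88 evaluable per group gives 85.9% power at 0.5 SD.

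Move the circumferences to secondary and report within-arm pre-post changes as descriptive only. Maintenance of weight loss may stay as a later step of the same sequence, which respects the abstract and the primary aim. Use the same wording in the abstract, the outcomes section and the sample-size paragraph.

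One limit should be stated. The Background section hypothesises that en_línea is better than, or at least similar to, group therapy. A non-significant difference at the second step would not show similarity.

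The cost is a protocol and registry amendment during recruitment. The Randomization and blinding section reports that no analysis has been done, so the change can still precede the results. Circumference and within-arm results can no longer be called primary. The fixed order keeps the stated alpha, so multiplicity adds no patients.

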#### Secondary outcomes measures

To determine the effectiveness of the different interventions following results will be considered for each intervention arm: 1) Adherence: at least 80% of completed website activities and 80% of self-records; 2) Drop out: Participants must finish the treatment; 3) Quality of life: significant differences between pre-post and follow-ups measures. Moreover, significant differences between the three interventions for the three variables aforementioned.

At the end of the study, participants will receive an email with a satisfaction questionnaire with the website and the mobile application, with an available space to make improvement suggestions.

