A randomized controlled trial (RCT) is need to examine the effectiveness of *en_línea* comparing with a standard primary care group therapy and a control group. All conditions will be described later in detail. We hypothesize that *en_línea* group will obtain better or, at least, similar effectiveness results than the standard therapy group, and better results than the control group. The primary aim of the RCT will be determine the effectiveness weight loss and maintenance of *en_línea* with the two comparison groups. The secondary objectives to determine the effectiveness of *en_línea* in comparison with the other conditions will be: a) the adherence to intervention, i.e. website tasks and mobile application records; b) number and stage of drop outs. We will conduct a 17 weeks, parallel-group, randomized controlled trial. Randomization will be performed with a simple randomization with a 1:1:1 allocation ratio. The aims of this paper are to describe the development of *en_línea* program and the protocol for the RCT.

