#### Assessment instruments

The questionnaires used in the assessment phase, apart from a sociodemographic questionnaire ad hoc*,* will be the following in its Spanish version:
E-TONA structured interview: a self-reported adaptation for adults will be used. This tool was designed to assess behavioral eating habits, physical activity, sedentary behaviors and health problems in fathers and children [35]. Only the behavioral eating habits data will be used in this study. The items of this descriptive and no diagnostic interview are multiple or dichotomous choice.The Temperament and Character Inventory Revised (TCI-R) [36, 37]. 240 items answered in a 5-Likert scale (1 = completely false; 5 = completely true). It includes seven main dimensions, 4 temperaments and 3 characters, with their corresponding specific features.Bulimic Investigatory Test Edinburgh (BITE) [38, 39]. Self-reported 33 item questionnaire, designed to identify bulimic symptoms: presence of binge eating and symptoms severity. Items are answered on different Likert scales or dichotomous choice.Stages of Change for Weight Management (S-Weight) [40]. Questionnaire of 5 excluding items to classify participants in one of the 5 stages of change for weight management.Process of Change for Weight Management (P-Weight) [40]. 33 items answered in a 5-point Likert scale to assess attitudes and behaviors to control weight.Night Eating Questionnaire (NEQ) [41, 42]. Self-reported 14 items scale to assess behavioral and psychological symptoms of Night Eating Disorder.SF-36 Health Survey (SF-36) [43, 44]. 36 items to assess functional health and wellbeing from the perspective of the respondent. It includes 8 scales related with the main aspects of heath, both physical and mental health.Coping Inventory Strategies (CSI) [45, 46]. 40 items tool answered on a 5-Likert scale (0 = not at all; 4 = totally), to assess 8 different coping strategies.Dutch Eating Behavior Questionnaire (DEBQ) [47, 48]. 33 item questionnaire answered in a 5-point Likert scale (1 = never; 5 = very often), to assess different types of intake.Depression Anxiety Stress Scale (DASS-21) [49, 50]. 21 item questionnaire answered in a 5-point Likert scale (0 = nothing applicable to me; 5 = applicable to me most of the time), to evaluate the severity of depression, anxiety and stress experimented during the last week.

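### Secondary outcomes are given the task of determining effectiveness by significance, including within-arm change, with no lead quality-of-life score or time point fixed

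*Protocol article*

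**What the plan says.** The Secondary outcomes measures section opens with "To determine the effectiveness of the different interventions following results will be considered for each intervention arm". It then lists adherence, dropout and quality of life. For quality of life the criterion is a significant change from before to after treatment and at the follow-ups, judged within each arm. The section then adds "significant differences between the three interventions for the three variables aforementioned".

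The Background uses similar language, "The secondary objectives to determine the effectiveness of", but lists only two objectives there: adherence and dropout. Quality of life appears as a secondary outcome in the Abstract and in the Outcomes section.

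Of the SF-36, the Assessment instruments section says "It includes 8 scales related with the main aspects of heath, both physical and mental health". It names no lead scale or summary score. The Control group section states that quality of life is reviewed in all arms at 1, 3, 6 and 12 months after the post-treatment session.

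Under Statistical analysis, a repeated-measures ANOVA "will be conducted to analyze primary and secondary outcomes". The only alpha in the document is in the sample-size paragraph for weight loss: "The range of the effect size of the intervention will be 0.5 SD in group comparisons, alpha 5% and two-tail tests".

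**The concern.** A secondary outcome normally supports the primary result. Here the text under that label gives these outcomes an inferential role: significance on them is how effectiveness is to be judged. Two problems follow.

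- **Several outcomes, none leading.** If each outcome or scale is tested separately, an isolated significant result can arise by chance well above 5% of the time and be presented as evidence of effectiveness.
- **Within-arm significance.** A significant change inside one arm says nothing about the arms' relative effect. All arms can improve together. Even the control arm receives a newsletter and self-recording material.

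A null or mixed weight result could then be accompanied by an effectiveness statement resting on one quality-of-life scale or on a change in one arm.

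**Working it through.** The plan states no family-wise error rate for the secondary outcomes, so there is no figure to reproduce.

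**Inputs from the protocol article**
- Three arms, allocated 1:1:1, so 3 pairwise contrasts.
- Eight SF-36 scales (Assessment instruments).
- Two further outcomes, adherence and dropout, giving 8 + 2 = 10 outcomes.
- Five times after baseline: post-treatment and 1, 3, 6 and 12 months.
- Arm size 88 ("These data determine that we need at least 88 patients per group") and dropout 31% ("considering an expected 31% dropout rate").

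**Assumptions not in the document**
- Quality of life is scored as the eight SF-36 scales.
- Each test is two-sided at 5%.
- Correlation is 0 to 0.7 between scales and 0.5 to 0.7 between visits.
- Adherence is 50% in every arm. Adherence and dropout are independent of the scales.

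**Independent tests.** The chance of at least one false positive among m tests is 1 − 0.95^m.
- m = 10 (one overall three-arm test per outcome): 1 − 0.95^10 = 40%.
- m = 9 (adherence left out): 1 − 0.95^9 = 37%.
- m = 3 (one lead quality-of-life score, adherence, dropout): 1 − 0.95^3 = 14%.

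**Correlated scales.** A simulation was run with no true differences and 1,500 runs per setting. The simulation standard error near 33% is √(0.33 × 0.67 / 1,500) = 1.2 percentage points. The overall test for each scale compared the three arms on each participant's mean over the five times. It stands in for the single between-arm test of a repeated-measures ANOVA. Each cell gives the results at between-visit correlation 0.5 / 0.7.

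| Correlation between scales | 8 scales, one overall test each | 10 outcomes, one overall test each | 10 outcomes, three ungated pairwise tests each | Overall test per scale at each time, plus the 2 binary outcomes (42 tests) |
|---|---|---|---|---|
| 0 | 35% / 35% | 41% / 41% | 73% / 75% | 84% / 77% |
| 0.3 | 30% / 32% | 37% / 38% | 68% / 70% | 78% / 71% |
| 0.5 | 26% / 25% | 33% / 32% | 64% / 62% | 74% / 63% |
| 0.7 | 20% / 20% | 27% / 27% | 54% / 56% | 61% / 54% |

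The smallest reading of the stated analysis, one overall test per outcome, gives 27% to 41%. For the eight scales alone it gives 20% to 35%. Pairwise tests read only after a significant overall test cannot raise these rates, because each still needs that overall result. The last two columns need tests that the Statistical analysis section does not describe.

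**Within-arm criterion.** This needs no simulation. If every arm changes by the same amount, the between-arm effect is zero, yet a large enough common change is significant in each arm. The criterion is met while the arms do not differ.

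**The case against.** The strongest reply is that testing order, alpha rules and the choice of a lead scale for secondary outcomes commonly belong in a statistical analysis plan or full protocol, and neither is shown. That is right, and the absence of an adjustment is not the fault here. The fault is the role that the article itself assigns to these outcomes, which an unseen plan would have to contradict.

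Several further points stand and limit the claim.
- Weight loss is clearly primary and alone drives the sample size. The article says that the secondary results will be considered. A reader might infer that any one significant scale, in any pair of arms at any visit, establishes effectiveness, but no sentence says so.
- A reader might infer that a false claim is more likely than not. That needs ungated pairwise or separate per-visit tests, whereas the stated ANOVA handles the visits in one model.
- A reader might infer that 5% is fixed for every secondary test. It is stated only for sizing the trial.
- The Background's effectiveness wording covers adherence and dropout, so it does not support the quality-of-life argument.
- That the SF-36 is the quality-of-life measure at follow-up is inferred. The article lists it for the assessment phase and names no instrument for the follow-up visits.
- Adherence is defined partly by website activities, which only the online arm has. A difference between arms there may be structural, and a multiplicity rule would not address it.

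**Conclusion.** The concern holds in a limited form. The article assigns significance on secondary outcomes the task of determining effectiveness, counts within-arm change towards it, and fixes no lead quality-of-life score or time point. Under the assumptions above, the chance of at least one false between-arm result is about 27% to 41% with one overall test per outcome. That is well above 5% but below one half. Rates above 50% depend on a testing practice that the article does not specify. The within-arm problem rests on none of these numbers. It follows directly from the stated criterion.

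**What to change.** In Secondary outcomes measures, replace the opening clause with a statement that the secondary outcomes are supportive, are reported as between-arm estimates with 95% confidence intervals, and carry no effectiveness claim of their own. Present changes within each arm descriptively.

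If the sponsor wants one quality-of-life claim, name in advance one score, one between-arm contrast and one time point, and test it only after the primary weight comparison is significant. This step is optional, and other schemes that control the error rate would also serve.

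The cost is a paragraph of wording, with no new patients or data. The Randomization and blinding section reports that recruitment is under way and that nothing has been analysed, so the change can be made without sight of results. The price is that isolated significant secondary results can no longer be reported as proof of effectiveness.

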**Fig. 2 Fig2:**
[figure not shown]
Overview of *en_línea* program content

“Set weekly goals” and “Verifying weekly goals” sections are aimed to adjust expectations and establish realistic goals. If the participants, at the end of the week, verify the accomplishment of 75% of the initial weekly goals, they will receive an automatic congratulation message and they should reward themselves.

Participants will download a mobile application designed exclusively for *en_línea*. They should record their daily meals, at least five records per day; their daily physical activity, at least their daily steps; and, their weekly weight. To count their daily steps participants will use commercial mobile applications.

Finally, once a week a specialized psychologist will provide personalized feedback about the activities of the website and the mobile application records. There is a space for this feedback at the end of each section of the website. The participant can review each activity with the corresponding feedback. Participants can send an email to the psychologist to solve doubts.

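### Adherence is defined only by a joint 80%/80% pass mark and then tested between arms, which discards graded information on a criterion whose website half is described for one arm only

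*Protocol article*

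**What the plan says.** Under Secondary outcomes measures, the protocol lists as the first result for each arm: "Adherence: at least 80% of completed website activities and 80% of self-records". Drop-out and quality of life follow. The paragraph then adds: "Moreover, significant differences between the three interventions for the three variables aforementioned". Adherence is one of those three variables, and no percentage-scale adherence endpoint appears anywhere else.

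The Background states the objective without a cut, as "the adherence to intervention, i.e. website tasks and mobile application records". The en_línea description sets out what app users are asked to enter: "They should record their daily meals, at least five records per day; their daily physical activity, at least their daily steps; and, their weekly weight". The Standard group therapy section provides self-recording on paper. The Control group section provides self-record material and a newsletter. Neither of those two sections gives a number of records, and neither describes website activities.

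The Statistical analysis section says that a repeated-measures ANOVA "will be conducted to analyze primary and secondary outcomes". It names no method for a yes/no outcome.

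**The concern.** A two-part pass mark turns a finely graded quantity into one bit. A participant who completes 79% of the records counts the same as one who completes none, and 80% counts the same as 100%. The protocol gives no source or reason for the 80% level.

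Adherence is the first secondary objective, and the Discussion expects the programme to do better on it. If the arms are compared on the pass mark, a real difference in how much people record is more likely to be missed, and a null result could be misread as equal adherence. A further difficulty is that participants without website activities cannot be scored on the website half, so the criterion as written has no defined value in two of the three arms.

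**Working it through.** **1. How graded the quantity is.** 17 weeks is 17 × 7 = 119 days. With at least 5 meal records and 1 activity record a day plus a weekly weight, an en_línea participant is asked for at least 119 × 6 + 17 = 731 entries.

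**2. The plan's own figure.** The sample size rests on weight loss: "To estimate the sample size has been used the primary outcome, weight loss differences between baseline and post-treatment measures". Its inputs are "The range of the effect size of the intervention will be 0.5 SD in group comparisons, alpha 5% and two-tail tests", giving "we need at least 88 patients per group". Power is not stated. For two arms, power = Φ(d√(n/2) − 1.96). With d = 0.5 and n = 88 this is Φ(0.5 × 6.633 − 1.96) = Φ(1.357) = 91.3%. A 90% target needs 85 per group (normal) or 86 (t), so 88 is close to a 90% design. None of this was set for adherence.

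**3. Sample sizes used.** 88 is the stated number per group. 305/3 = 101.7 is the number randomised per arm. 305 × 0.69/3 = 70.2 is the number left per arm after the expected 31% dropout. (That 305 does not follow from 88 and 31%, since 264/0.69 = 383, is a separate matter.)

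**4. Cost of a single cut, normal score.** Let p0 be the pass rate in the lower arm. The other arm's rate is p1 = Φ(Φ⁻¹(p0) + d). With p̄ the mean of the two, power = Φ{[(p1 − p0) − 1.96√(2p̄(1 − p̄)/n)] / √([p0(1 − p0) + p1(1 − p1)]/n)}.

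Example with d = 0.5, n = 88, p0 = 0.50: p1 = 0.691, and power = Φ[(0.1915 − 0.1450)/0.0726] = Φ(0.64) = 73.9%. The loss is 91.3 − 73.9 = 17.4 points.

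Loss in percentage points, by lower-arm pass rate:

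| n per arm | d (SD) | Power, full scale | 10% | 20% | 40% | 50% | 70% | 80% |
|---|---|---|---|---|---|---|---|---|
| 70 | 0.3 | 42.7% | 23.2 | 17.7 | 13.8 | 13.9 | 17.5 | 21.3 |
| 70 | 0.5 | 84.2% | 36.6 | 25.1 | 19.1 | 20.2 | 29.2 | 38.5 |
| 70 | 0.6 | 94.4% | 30.5 | 18.8 | 14.0 | 15.4 | 25.5 | 36.6 |
| 88 | 0.3 | 51.2% | 27.7 | 20.9 | 16.1 | 16.3 | 20.7 | 25.4 |
| 88 | 0.5 | 91.3% | 34.5 | 22.2 | 16.3 | 17.4 | 26.5 | 36.6 |
| 88 | 0.6 | 97.8% | 24.0 | 13.2 | 9.3 | 10.4 | 19.2 | 30.0 |
| 101.7 | 0.3 | 57.1% | 30.7 | 22.9 | 17.6 | 17.7 | 22.7 | 28.0 |
| 101.7 | 0.5 | 94.6% | 31.6 | 19.3 | 13.7 | 14.7 | 23.5 | 33.8 |
| 101.7 | 0.6 | 99.0% | 19.1 | 9.6 | 6.4 | 7.3 | 14.8 | 24.9 |

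The range is 6.4 to 38.5 points; results at 0.4 SD fall inside it. At 0.8 SD and n = 88 the best-placed cut loses only 1.1 points.

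**5. Joint cut.** This assumes both components exist in both arms, a bivariate normal score with 0.5 SD on each component, correlation 0.3 to 0.9, component pass rates of 30% to 70%, and n = 88. The loss is 6.7 to 21.2 points against one continuous score, and 13.9 to 23.3 against the mean of the two.

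**6. A different shape.** Suppose participants are either completers, with scores from Beta(18,2), or early stoppers, with scores from Beta(1,4); these shapes are assumed. In 8,000 simulated trials at 88 per arm, 30% against 53% completers gave 83.5% power for the t-test and 83.3% for the 80% cut. With 20% against 40% completers, the cut did slightly better (about 79% against 76%). Smooth U-shaped distributions lost 17 to 39 points.

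**The case against.** The strongest reply is that the yes/no coding is inferred. The protocol never says that each participant is classed before the arms are compared. The primary outcome has a similar layout, with a 5–10% success definition beside a comparison of weight loss itself. The objective carries no cut, and ANOVA is named for the secondary outcomes. The 80% could be a descriptive benchmark. This stands in part: the pass/fail reading is natural but not explicit. The ANOVA does not settle it, because the same sentence covers drop-out, which is plainly binary. The primary outcome names weight loss as the measure beside its success definition, whereas adherence has only the threshold.

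A reader might infer that the cut costs at least 17 points of power. The documents do not support that floor. The 0.5 SD and the 88 per group belong to weight loss, and the loss is smaller with a better-placed cut, a larger sample or a larger difference. With an expected 31% dropout, a completer/stopper split is also plausible, and there the loss can vanish.

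A reader might also infer from the Background's remark on low adherence in web programmes that few will reach 80%. That remark is comparative, and the same paragraph reports better results with professional feedback, which en_línea includes.

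Finally, comparing percentages is not simply a rewording. Only en_línea has a numeric recording requirement, and nothing says that control participants return their records. This stands, and the fix has to deal with it.

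**Conclusion.** The point holds as a minor one. The only adherence measure under Outcomes is a joint threshold, arms are to be tested on that variable, and the website part is described for one arm only. On the natural reading, graded information is thrown away; for a normal score and a small shift, a cut keeps at best about 2/π = 64% of the efficiency.

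The size is illustrative. It is roughly 6 to 39 points of power for a normal score, an assumed 0.3 to 0.6 SD difference, 70 to 101 per arm and lower-arm pass rates of 10% to 80%. It is about 1 point at 0.8 SD with a well-placed cut, and can be nil under a completer/stopper split. The protocol claims no power for adherence, so no stated figure is wrong.

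**What to change.** In Secondary outcomes measures, make the between-arm adherence measure the percentage of expected self-records completed over the 17 weeks, for every randomised participant, with records not made counted as zero. Define the denominator the same way in all arms, for example the percentage of days with the requested meal and exercise record. State how the control arm's records are collected; otherwise a zero could mean not returned rather than not made. Compare arms by mean difference with a robust or bootstrap confidence interval. Report website completion descriptively for en_línea only, and keep the proportion reaching 80% as a descriptive summary.

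The cost is that paper records must be counted and the control arm's records returned. The 80% self-record rule already requires both, since the percentage must be known to apply it. The protocol reports that recruitment is under way and that no analysis has been done, so the change can be made before results are seen.
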